#### 945 **IX.4. Secondary analyses**

946 QoL will be assessed by two validated questionnaires (EORTC QLQ-C30 and HN35) at different  
 947 measurement times. Changes in quality of life will be studied in accordance with recent work (47). A  
 948 difference of at least 10 points will be considered the smallest difference of clinical significance.  
 949 Sensitivity analyses with a difference of at least 5 points will be performed.

950 For the different endpoints studied, a longitudinal study will be proposed by considering mixed  
 951 models to take into account inter- and intra-patient variability ('random intercept' and 'slope' effects).  
 952 These analyses will thus propose to study the (fixed) group effects (sex, age, anatomical pathological  
 953 criteria...), evaluation time and their interaction while taking into account the center and subject  
 954 effects as well as random in order to model inter- and intra-patient variability on the one hand and  
 955 inter- and intra-center on the other hand. More precisely, to compare the means of the quantitative  
 956 criteria between the inclusion and each measurement time, a linear mixed-effects model of the cLDA  
 957 (constrained Longitudinal Data Analysis) type will be used. In this model, the variable to be explained  
 958 includes both the baseline and post-inclusion values and the mean baseline difference between the  
 959 groups is constrained to 0. This model makes it possible to calculate the changes between the  
 960 inclusion and each follow-up time while adjusting on the values at inclusion. The difference between  
 961 each group at each time is given through the interaction between the time and the randomization arm.  
 962 The model will include different random effects: at the patient level (model with y-intercept and  
 963 random slope allowing variation between patients in baseline values as well as changes in the outcome  
 964 over time) and at the center level. The model parameters will be estimated using the Restricted  
 965 Maximum Likelihood (REML) method.

#### 966 **IX.5. Method of accounting for missing, unused or** 967 **invalid data**

968 Particular attention will be paid to missing data. A sensitivity analysis will be performed to investigate  
 969 the attrition bias, i.e. the quantity (level of attrition) and the nature (independence from the

randomization group) of the missing data in order to propose the most appropriate data imputation method (maximum bias, multiple imputation, Verbeke and Molenberghs estimate).

## IX.6. Responsible for analysis

All statistical analyses will be performed with the *Stata software* (version 13, StataCorp, College Station, USA) in accordance with the recommendations of the *International Conference on Harmonization-Good Clinical Practice*. An analysis plan will be drawn up before the database is frozen.

The persons responsible for the statistical analysis are:

[name] [name] ([contact]; [contact])

[name] [name] ([contact]; [contact])

## X. INDEPENDENT OVERSIGHT COMMITTEE

The *Independent Data and Safety Monitoring Committee (IDSMC)* will conduct a review of all safety data from the trial and all events identified as requiring potential advice. It will be composed of 3 experts: 2 radiotherapists and 1 statistician/methodologist. The experts conducting this review will be selected for their expertise in clinical research and in the field of the study and will conduct an independent review. The IDSMC may propose modifications to the protocol (eligibility criteria, dose, etc.), premature termination of the trial, etc. Its opinion is advisory to the Promoter, who is responsible for making the final decision on the implementation of the recommendations proposed by this committee.

Since the primary objective of this study is evaluated at 2 years, once 30 patients have been included (33% of inclusions), a review of all grade  $\geq 3$  toxicities will be reported to the IDSMC. The grade 4 toxicity rate is expected to be less than 10%. Inclusions will not be stopped during this evaluation.

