### V.3.3 Discontinuation of the study

The end of the study is expected when the last patient has completed their follow-up at 2 years. The study may be stopped prematurely if the toxicity is too high or the inclusion rate is too low. The independent oversight committee will make its recommendations. It is the developer who will decide on the stoppage.

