### IX.1. Number of topics to include

881 To determine the number of patients needed, two objectives were considered: severe late toxicity at  
882 2 years (primary outcome) and local control rate at 2 years (secondary outcome). The experimental  
883 design follows a one-step Fleming design with no intermediate analysis due to the primary endpoint  
884 which will be evaluated at 2 years (severe late toxicity).

885 The safety and efficacy profile of hypofractionated stereotactic radiotherapy of the operative bed is  
886 expected to be equivalent to other radiotherapy techniques (brachytherapy or normofractionated  
887 IMRT) (cf 3. Rationale of the study for details). In brachytherapy, the rate of late soft tissue ulceration  
888 is around 10-20% and the rate of bone necrosis is around 5-10%. We have decided: 1/ to accept a rate  
889 of less than 5% and 2/ to reject a rate of more than 15%. With a unilateral test for significance ( $\alpha=0.05$ )  
890 with a power of 90% ( $\beta=0.10$ ), the minimum number of patients to be included is 67.  
891 Hypofractionated stereotactic radiotherapy of the operative bed will then be considered an  
892 unacceptable treatment if 6/67 patients (9%) or more have severe late toxicity (grade  $\geq 3$ ).

893 The local control rate of hypofractionated stereotactic radiotherapy is expected to be equivalent to  
894 other radiotherapy techniques (brachytherapy or normofractionated IMRT). We have decided: (i) to  
895 accept a rate of more than 90% and (ii) to reject a rate of less than 80%. With a one-sided significance  
896 test ( $\alpha=0.05$ ) with a power of 80% ( $\beta=0.20$ ), the minimum number of patients to be included is 83.  
897 A lower potency was decided for control as a secondary outcome. Hypofractionated stereotactic  
898 radiotherapy of the operative bed will then be considered an acceptable treatment if 72/83 patients  
899 (87%) or more are locally controlled at 2 years.

900 As a result of these results, and to compensate for possible loss to follow-up, a total of 90 patients  
901 will be included in this study.

902 As the primary objective of this study is estimated at 2 years, once 30 patients have been included  
903 (33% of inclusions), a review of all grade  $\geq 3$  toxicities will be communicated to the independent trial  
904 monitoring committee (IDSMC = *Independent Data and Safety Monitoring Committee*). The grade 4  

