### ***XI.1.3 Adverse Reaction***

The adverse reaction of a search is any adverse event due to the research.

Serious adverse reactions are classified into the following subclasses:

- Expected adverse reactions

Expected serious adverse reaction : when already mentioned in the most recent version of the protocol. In this protocol, the expected side effects are those due to stereotactic radiotherapy:

Acute:

- ❖ Mucositis
- ❖ Epidermatitis
- ❖ Dysphagia that may require in some cases the placement of a feeding tube in the stomach
- ❖ Xerostomia (saliva may be thicker at first and then become rarer with dry mouth. Improvement in saliva can be seen up to two years after radiotherapy).
- ❖ Dysgeusia, ageusia
- ❖ Mucosal ulcerations

Late:

- ❖ Mandibular osteonecrosis (expected rate< 5-10%) (Special attention should be paid to dental care)
- ❖ Soft tissue necrosis (expected rate< 10-20%)
- ❖ Fibrosis

- Unexpected serious adverse reaction:

if its nature, severity or course differs from those described in the most recent version of the Investigator's Brochure or the Summary of Product Characteristics for a medicinal product or the Instruction Leaflet for a medical device.

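### The one scheduled IDSMC review is triggered by 30 inclusions, with no follow-up requirement, and its only reference figure is a grade 4 rate, while the primary event is late grade ≥3 toxicity

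*Protocol*

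**What the plan says.** Protocol IX.1 and X describe the same review in nearly the same terms. It takes place "once 30 patients have been included", a third of the planned 90, and the reason given is that the primary objective is only evaluated at 2 years. All grade ≥3 toxicities are sent to the committee. The one number attached is "The grade 4 toxicity rate is expected to be less than 10" per cent. Accrual continues: "Inclusions will not be stopped during this evaluation". Section X also gives the committee a general remit over the trial's safety data and "all events identified as requiring potential advice", without dates.

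The primary endpoint (IV.1) is the rate of patients with grade ≥3 toxicity linked to the radiotherapy and occurring more than 3 months after it ends, assessed at 2 years. IX.1 designs for less than 5% against more than 15% and calls the regimen an "unacceptable treatment if 6/67 patients (9%) or more have severe late toxicity". VI.1 and IX.1 rule out an interim analysis. V.3.3 adds "The study may be stopped prematurely if the toxicity is too high", on the committee's advice and with no number.

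**The concern.** The review is the only scheduled occasion on which the independent committee looks at toxicity, and it is justified by the lateness of the primary endpoint. Two features do not match that endpoint.

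- **Reference figure.** It concerns grade 4 only and has no time window. The trial is judged on grade 3 and worse, in the late window.
- **Trigger.** It counts patients included, whatever follow-up they have. The endpoint needs time after radiotherapy before an event can count at all.

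At stake is the quality of the advice on which V.3.3 relies. The committee would have mostly acute data and no benchmark for the event that decides the trial. The remaining 60 patients would then be enrolled with no further IDSMC review scheduled.

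**Working it through.** **The protocol's own figures.** One-stage Fleming formula, 5% against 15%, one-sided α = 0.05, power 90%:

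n = [(1.645·√(0.05·0.95) + 1.282·√(0.15·0.85)) / 0.10]² = 66.6, so 67.

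This reproduces IX.1. The failure limit 6/67 is 8.96%, the stated 9%.

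**Reference figure.** In 30 patients, below 10% means at most 2 grade 4 events (2/30 = 6.7%; 3/30 = 10.0%).

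- Two grade 4 plus three grade 3 events give 5/30 = 16.7% grade ≥3, above the 15% design rate, and the expectation is still met.
- Any further number of grade 3 events would leave it met.
- Suppose the true grade ≥3 rate is 15%, follow-up is complete, and grade 4 makes up 25–50% of these events (an assumption). The grade 4 rate is then 3.75–7.5%, and P(≤2 of 30) is 0.90–0.61.

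**Timing: inputs.** 90 patients in 48 months (VI.6), accrual taken as even. The lag L from inclusion to end of radiotherapy is taken as 0.4–1.4 months: treatment lasts 11–13 days, and the work-up may precede it by up to 28 days (VI.3). The late window runs from 3 to 24 months after radiotherapy, 21 months per patient. No death, recurrence or loss is allowed for.

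**Timing: results.**

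- Accrual rate 90/48 = 1.875 per month; 30th inclusion at 30/1.875 = month 16.
- Patients in the late window: 1.875·(16 − L − 3) = 23.6 (L = 0.4) to 21.8 (L = 1.4), so 22–24 of 30.
- Patients with 24 months of follow-up: 0, since the study is 16 months old.
- Late person-months observed: 1.875·(13 − L)²/2 = 149 to 126, of 30·21 = 630, or 24% to 20%.
- Expected late events, constant hazard h = −ln(1 − p)/21 over the 21 months: 0.9–1.1 at p = 15% and 1.6–1.9 at p = 25%.

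**Sensitivity to accrual.** If the first 30 took 24 months instead of 16 (hypothetical), the observed share with L = 0.9 would be (24 − 0.9 − 3)²/(2·24·21) = 404/1008 = 40%, still with nobody at 24 months after radiotherapy.

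**What later looks would add** (same 30 patients, L = 0.9):

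| Look | Study month | Mean late time per patient | Share of 21 months | Still to enrol |
|---|---|---|---|---|
| 30th patient 6 months after radiotherapy | 22.9 | (3 + 19)/2 = 11.0 | 52% | 90 − 42.9 ≈ 47 |
| 30th patient 12 months after radiotherapy | 28.9 | [(21² − 9²)/2 + 4·21]/16 = 16.5 | 79% | 90 − 54.2 ≈ 36 |

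**Cost in false concern.** With complete follow-up, 3 or more grade ≥3 events in 30 occur with probability 0.19 at a true rate of 5% and 0.85 at 15%.

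**The case against.** The strongest reply is that the 10% is an expectation and no decision rule hangs on it. The committee receives every grade ≥3 event and includes a statistician. If the true grade ≥3 rate were 30%, complete follow-up of 30 patients would show 3 or more such events with probability 0.998, and the committee would see them. The probabilities of meeting the grade 4 figure therefore describe a test that the protocol does not define. An early safety look is also consistent with a one-stage design whose endpoint matures at 2 years. All of this stands, and it limits the point to a missing benchmark and a missing follow-up condition.

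Stronger readings that a reader might infer are not supported:

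- **That 10% for grade 4 is simply laxer than the 9% failure limit, so that a rate between the two would pass.** No count in 30 lies between 9% and 10%. The two figures also differ in scope: the 10% is untimed and names no attribution, while the 9% is late and radiotherapy-related.
- **That late toxicity goes unreviewed on any schedule.** Serious events are notified without delay until 2 years after radiotherapy (XI.2.1, XI.2.3), and an annual safety report goes to the ANSM and the CPP (XI.2.4). The gap concerns the IDSMC, whose wider remit in section X has no dates.
- **That the expected rates in XI.1.3, such as "Soft tissue necrosis (expected rate< 10-20" per cent, contradict the 5%/15% design.** Those rates carry no grade, and the general example of more frequent serious reactions under Developments is not tied to them.

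**Conclusion.** The point holds in a limited form. The one scheduled IDSMC review has a trigger without a follow-up condition, and a reference figure that leaves out grade 3 and grade 5 and has no time window. Neither matches the primary endpoint.

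Under even accrual, the review sees about a fifth to a quarter of the late person-time of its 30 patients and about one late event at the 15% design rate, so it is mainly a look at acute toxicity. The month, the person-time share and the event counts rest on even accrual, the assumed lag, a constant hazard and no attrition. A slower start would raise the share. The 16.7% example rests on none of these.

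The primary analysis and the sample size are untouched. This is an inexpensive improvement to safety oversight; it does not show that the committee would miss a failing treatment.

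**What to change.** In IX.1 and X:

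- Keep the look at 30 included as the acute-toxicity review.
- Reconcile its reference figure with the primary endpoint. List treatment-related grade ≥3 events, including grades 4 and 5, with acute and late shown separately and denominators by follow-up reached. Place them beside the protocol's own 5% and 15% rates, stated to be an advisory reference and not a stopping boundary.
- Schedule one or two further looks at the same 30 patients, for example when the 30th is 6 and 12 months after radiotherapy, without suspending inclusions.

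The XI.1.3 expected rates need no change for this purpose.

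The cost is an amendment and one or two extra listings or meetings, using late-toxicity data already collected at the 3-monthly visits (VI.5.2). There is some chance of false concern: 0.19 at a true 5% rate for 3 or more of 30, for a single look with complete follow-up. The combined figure for repeated looks has not been worked out and should be, before the wording is fixed.

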## XI. SECURITY ASSESSMENT – ADVERSE EVENT MANAGEMENT

### XI.1. Definitions

#### XI.1.1 Adverse Event

An adverse event (AE) is defined as any adverse event that occurs in a person who is engaged in research involving humans, whether or not the adverse event is related to the research or the product that is the subject of the research

1000

1001 ***XI.1.2 Serious adverse event or reaction***

1002 A serious event is an event:

- 1003 - whose course is fatal,
- 1004 - or that endangers the life of the person who is involved in the research,
- 1005 - or that results in a significant or lasting disability or disability,
- 1006 - or that causes hospitalization or a prolongation of hospitalization
- 1007 - or that results in a congenital anomaly or malformation
- 1008 - or any other event that does not meet the qualifications listed above, but may be considered
- 1009 "potentially serious", including certain biological abnormalities
- 1010 - or medically relevant event in the judgment of the investigator

1011 Certain circumstances requiring hospitalization do not fall under the criterion of seriousness:

1012 "hospitalization/prolongation of hospitalization" such as:

- 1013 - Admission for social or administrative reasons
- 1014 - Protocol-predefined hospitalization
- 1015 - hospitalization for medical or surgical treatment scheduled prior to research
- 1016 - Passage to day hospital

1017

1018 The expression "*which endangers the life of the person*" is reserved for an immediate life-threatening  
1019 threat, at the time of the adverse event, regardless of the consequences of corrective or palliative  
1020 therapy.

1021 The term "*disability*" or "*incapacity*" refers to any clinically significant disability, whether temporary  
1022 or permanent.

1023 Deaths, regardless of their cause, including when they correspond to a progression of the disease  
1024 being treated, are considered serious events.

1025 Other events that do not meet the above qualifications may be considered "*potentially serious*",  
1026 including certain biological abnormalities. The medical judgment of the investigator or sponsor may  
1027 lead to the reporting of such events in the same manner as "serious" events.

1028

1029 Some events not to be considered serious in this study:

1030 Disease progression should not be considered a SAE.

1031 Due to the severity of the disease in this study, certain conditions defined as SAEs will be excluded  
1032 from the SAE reporting procedure, namely:

- 1033 ❖ Scheduled hospitalization prior to the start of the trial
- 1034 ❖ Hospitalization or surgery related to the treatment of the disease
- 1035 ❖ Any event occurring between the signing of the consent and the performance of

stereotactic radiotherapy

- ❖ Deaths related to disease progression.

### ***XI.1.3 Adverse Reaction***

The adverse reaction of a search is any adverse event due to the research.

Serious adverse reactions are classified into the following subclasses:

- Expected adverse reactions

Expected serious adverse reaction : when already mentioned in the most recent version of the protocol. In this protocol, the expected side effects are those due to stereotactic radiotherapy:

Acute:

- ❖ Mucositis
- ❖ Epidermatitis
- ❖ Dysphagia that may require in some cases the placement of a feeding tube in the stomach
- ❖ Xerostomia (saliva may be thicker at first and then become rarer with dry mouth. Improvement in saliva can be seen up to two years after radiotherapy).
- ❖ Dysgeusia, ageusia
- ❖ Mucosal ulcerations

Late:

- ❖ Mandibular osteonecrosis (expected rate< 5-10%) (Special attention should be paid to dental care)
- ❖ Soft tissue necrosis (expected rate< 10-20%)
- ❖ Fibrosis

- Unexpected serious adverse reaction:

if its nature, severity or course differs from those described in the most recent version of the Investigator's Brochure or the Summary of Product Characteristics for a medicinal product or the Instruction Leaflet for a medical device.

### ***XI.1.3 Developments***

New fact: any new data that may lead to a re-evaluation of the benefit-risk balance of the research or the product being researched, to changes in the use of that product, in the conduct of the research, or

1068 in documents relating to the research, or to the suspension or interruption or modification of the  
1069 protocol of the research or similar research.

1070 For example, we can mention:

- 1071 ❖ serious adverse reactions that are more frequent;
- 1072 ❖ the results of interim analyses, when they are relevant to the safety of people (in particular  
1073 insufficient effectiveness);
- 1074 ❖ serious adverse events related to clinical trial procedures;
- 1075 ❖ insufficient efficacy in life-threatening diseases;
- 1076 ❖ the results of animal studies that would provide new information on the safety of the  
1077 product;
- 1078 ❖ and in general, any new information that may lead to a re-evaluation, in an unfavourable  
1079 direction, of the risk/benefit ratio of the research.

1080

1081 **Any new fact** concerning the research (or the product used) and likely to affect the safety of the  
1082 persons who take part in the research will be the subject of appropriate urgent safety measures and  
1083 information without delay by the Promoter to the competent authority and the Committee for the  
1084 Protection of Persons.

1085

#### 1086 ***XI.1.4 Other event to be considered serious: pregnancy/breastfeeding***

1087 In general, pregnancy and breastfeeding are exclusion criteria from the study. If pregnancy occurs  
1088 during the study, the patient should be discharged from the study immediately. The patient should be  
1089 monitored throughout her pregnancy and after the birth of the child.

1090

## 1091 **XI.2. Reporting of serious adverse events**

### 1092 ***XI.2.1 Responsibility of the Investigator***

1093 For each type of research involving humans, the investigator records the adverse events or adverse  
1094 analytical findings defined in the protocol as decisive for the safety assessment, keeps a paper trail  
1095 and notifies them to the sponsor.

1096 The investigator is responsible for reporting all adverse events in the case report form.

1097 The severity or grade of the event should be assessed according to the toxicity criteria NCI-CTCAE-  
1098 v.4.03 (*Appendix 1*).

1099 The investigator shall inform the sponsor of all serious adverse events that have occurred in  
 1100 participants, unless otherwise provided for in the protocol.

1101 The investigator is responsible for the appropriate medical follow-up of patients until the resolution  
 1102 or stabilization of the event or until the patient's death. This may sometimes mean that this follow-up  
 1103 continues after the patient has been discharged from the trial.

1104 It transmits the additional information to the study's pharmacovigilance using a SAE reporting form.  
 1105 It also transmits the latest follow-up to the resolution or stabilisation of the SAE.

1106 It keeps the documents concerning the presumed adverse event in order to allow, if necessary, to  
 1107 complete the information previously transmitted.

1108 It responds to requests for additional information from pharmacovigilance in order to document the  
 1109 initial observation and implements the SPONSOR's decisions in relation to SAEs.

1110 The investigator shall notify the sponsor without delay from the day on which it becomes aware of  
 1111 any serious adverse event that has occurred in any patient included

- 1112 - - for the entire duration of the study (up to 2 years after the end of stereotactic radiotherapy),
- 1113 - After the trial has been stopped, regardless of the time limit, provided that no cause other than  
 1114 research can reasonably be incriminated,

1115 on a "Serious Adverse Event" form indicating the date of occurrence, intensity, relationship with the  
 1116 treatment (or research) evaluated, and follow-up.

1117 The narrative report must be completed and sent to the promoter as soon as new relevant information  
 1118 is obtained. Depending on the nature and severity of the event, copies of the patient's anonymized  
 1119 medical record may be attached, as well as the results of laboratory analyses.

1120 When a serious adverse event persists at the end of the study, the investigator will follow the patient  
 1121 until the event is considered resolved.

